# Influence of Early versus Late supplemental ParenteraL Nutrition on long-term quality of life in ICU patients after gastrointestinal oncological surgery (hELPLiNe): study protocol for a randomized controlled trial

**DOI:** 10.1186/s13063-019-3796-3

**Published:** 2019-12-27

**Keywords:** Supplemental parenteral nutrition, cancer, gastrointestinal surgery, quality of life, protein, ICU

## Abstract

**Background:**

Nutrition plays a major role in intensive care unit (ICU) treatment, influencing ICU length of stay and patient’s survival. If preferable enteral nutrition administration is not feasible, ESPEN and ASPEN guidelines recommend initiation of a supplemental parenteral route between the first and seventh day, but exact timing remains elusive. While rapid development in critical care enabled significant reduction in the mortality rate of ICU patients, this improvement also tripled the number of patients going to rehabilitation. Thus, it is quality of life after ICU that has become the subject of interest of clinicians and healthcare policy-makers. A growing body of evidence indicates that protein turnover in the early phase of critical illness may play a crucial role in the preservation of lean body mass. A negative protein balance may lead to muscle wasting that persists weeks and months after ICU stay, resulting in deterioration of physical functioning. Folliwing oncological gastrointestinal tract surgery, patients are threatened with negative protein turnover due to cancer and extensive surgical insult.

**Methods:**

This is a multi-centre, single-blinded, randomised controlled trial. The study population includes patients admitted to ICU units after major oncological gastrointestinal surgery that require supplemental parenteral nutrition. After initiation of enteral nutrition, the intervention group receives remaining daily requirement via supplemental parenteral nutrition on the first day of ICU stay while the control group is not supplemented parenterally until the seventh day of ICU stay while enteral nutrition is gradually increased.

Primary endpoint: long-term quality of life measured in the physical component score (PCS) of SF-36 questionnaire at 3 and 6 months after ICU admission.

**Discussion:**

To our knowledge, this is the first trial to investigate the influence of early supplemental parenteral nutrition on long-term quality of life after major oncological gastrointestinal surgery. We assume that, particularly in this population of patients, early supplemental parenteral nutrition may increase the long-term quality of life. The study construction also allows establishment of patients’ PCS SF-36 score prior to surgery and mean change in PCS SF-36 score during the recovery period, which is rarely seen in studies on critically ill patients.

**Trial registration:**

ClinicalTrials.gov: NCT03699371 registered on 12 October 2018.

## Background

### Overview

Nutrition plays a major role in intensive care unit (ICU) treatment, influencing not only ICU length of stay and in-hospital mortality but also the patient’s long-term quality of life. According to the American Society of Parenteral and Enteral Nutrition (ASPEN) and the European Society of Parenteral and Enteral Nutrition (ESPEN) the enteral nutrition (EN) route is preferential to the parenteral nutrition (PN) route to provide the daily protein and energy requirements for ICU patients (1.2–2 g protein/kg/day; 20–25 kcal energy/kg/day). However, in many cases, this cannot be met exclusively via EN due to a multitude of reasons. ASPEN and ESPEN guidelines then recommend the use of supplemental parenteral nutrition (SPN). Optimal timing of SPN remains elusive in the acute phase of critical illness (between first and seventh day after admission to ICU). A growing body of evidence underlines the crucial role of protein turnover in ICU patients [1].

### Existing knowledge

The importance of nutritional support is well established in the existing literature. Wischmayer et al. [2] raise awareness of the impact of interventions during ICU stay on long-term outcomes. The authors underline that, although rapid development in critical care enables a significant reduction in mortality rate, at the same time, it resulted in tripling the number of patients undergoing rehabilitation. Moreover, recent studies have proven that loss of lean body mass can reach a kilogram a day in critically ill or post-surgical patients [3]; most of this weight loss takes place during the first 7 days of ICU stay. However, the prevalence of fat tissue in the mass gained by patient following this may influence the future physical functioning after critical illness. Additionally, there are reports associating impaired wound healing, spontaneous wound development or even increased mortality secondary to pneumonia with extensive lean body mass loss [4]. It is worth noting that a catabolic/hypermetabolic state can persist for up to 2 years from hospital discharge and, although patients usually gain weight back after the ICU discharge, most of this weight is just fat mass.

Lately, the evidence on the role of optimal provision of protein in the prevention of muscle wasting is accumulating. Shifting the protein balance from negative to positive during the early stage of admission to ICU was proven possible by infusion of high level of amino acids (1 g/kg/day) [5]. Furthermore, the extent of the effect of the amino acid bolus, which was observed at the end of 3-h infusion, is present at 24 h [6]. Thus, these studies advocate that protein turnover remains stable even during critical illness. Moreover, studies on other populations (e.g. elderly, athletes) have proven that protein synthesis can be stimulated by bolus infusions [7, 8].

### Aim of the study

Our goal is to compare the influence of early and late SPN on the long-term quality of life (measured by the 36-Item Short Form Health Survey (SF-36) scoring system) in a population of critically ill patients after oncological surgery of the gastrointestinal tract at 3 and 6 months after admission to ICU.

### Hypothesis

We hypothesise that early goal-directed supplementation of proteins in SPN may significantly increase the number of points in the physical component score (PCS) at 3 and 6 months after admission to ICU in the population of critically ill patients after oncological surgery of the gastrointestinal tract.

### The need for the trial

Little is known about the effects of continuous low-dose protein administration on lean body mass in the early phase of critical illness. There are only a few studies on the impact of early protein delivery on long-term physical quality of life after ICU [9], whereas no studies assess this issue in a population of patients after oncological surgery of the gastrointestinal tract, who are highly threatened with a persistent catabolic state following the mixed effect of carcinogenesis and surgical insult. The potential benefits of this trial include not only the identification of factors that could alter the rate of individual physical impairments but it could also address the issue of growing costs of rehabilitation of ICU survivors to the healthcare system.

## Methods/design

### Study setting

The study will be conducted at the II Department of Anesthesiology and Intensive Care at the First Teaching Hospital in Lublin (Medical University of Lublin) and Department of Anesthesiology and Intensive Care at University Hospital of Opole (Medical University of Opole), Poland.

### Objective

This randomised trial will investigate the effect of an early supplemental nutrition therapy during intensive care, on long-term physical quality of life and short-term clinical outcomes.

### Trial design

Multi-centre, single-blinded, randomised controlled trial.

### Trial population

The trial population will include patients admitted to the ICU after major gastrointestinal surgery due to cancer who require SPN.

### Interventions

#### Intervention group

The intervention group will receive EN reaching up to 20% of daily nutritional requirements and early (on day 1 of their ICU stay) provision of up to 80% of their protein (2 g/kg/day or, in case of continuous renal replacement therapy (CRRT), 2.5 g/kg/day) and caloric (15–20 kcal/kg/day) needs in SPN, which will be continued until day 7 of ICU stay for the purpose of the study.

#### Control group

The control group will receive EN reaching up to 20% of their daily nutritional requirements and late provision (of up to 80%) of their protein (2 g/kg/day or, in case of CRRT, 2.5 g/kg/day) and caloric (15–20 kcal/kg/day) needs in SPN on day 7 of ICU stay if it is not already met via EN.

#### Route of administration

SPN is continuously infused for 24 h via central venous catheter. The central venous catheter is placed for routine medical purposes and therefore is not a part of any study-related procedure.

#### Dosage

SPN will be administered in a volume that provides up to 80% of the targeted proteins and calories. If energy is provided from other sources (e.g. via supplemental EN/oral nutrition or non- nutritional sources such as glucose solution for drug dilution or lipids from propofol), the dose of the SPN will be reduced accordingly. For dose calculation, the patient’s estimated body weight at the time of admission to the ICU will be used.

#### Administering of nutrition

The ICU nurses will administer the PN or EN according to the allocation. The SPN solutions will be prepared in a hospital pharmacy based on the ICU specialist’s prescription. The EN solutions are ready-to-use products prepared by manufacturers, details of which will be provided in the study report. Any problem related to nutrition will be reported by ICU nurses to ICU specialists. The site Principal Investigator is responsible for the adherence of administration of nutrition to the study protocol. Full and empty parenteral solution bags will be counted daily.

#### Concomitant care

The implementation of either the intervention or control group protocols will not require alteration to other usual care pathways. Relevant concomitant care will be recorded according to the study protocol.

### Outcomes

#### Primary endpoint

The long-term quality of life will be measured by the physical component of the 36-SF questionnaire assessed by a phone call at 3 and 6 months after admission to the ICU (License number QM047431 CT198126 OP073545 OGSR).

#### Secondary endpoints

A.During the 7-day treatment period in both treatment arms:
EN route intolerance (inability to administer up to 60% of protein needs on day 3 via EN route)Change from baseline in ultrasound measured thickness of diaphragm on days 1, 3 and 5 of ICU stayProtein deliveryEnergy intakeInsulin doseBlood glucose profileOrganic phosphorus levelB.During the 28-day treatment period in both treatment arms:
8.Change from baseline in the Sequential Organ Failure Assessment (SOFA) score9.Duration of mechanical ventilation10.Length of stay in the ICU11.ICU mortality12.Length of stay in hospital13.Hospital mortality14.New onset of hospital-acquired infection (defined according to the Centers for Disease Control and Prevention surveillance definition as a localised or systemic condition resulting from an adverse reaction to the presence of an infectious agent(s) or its toxin(s), with no evidence that the infection was present or incubating at the time of admission to the acute care setting)15.Antibiotic-free days

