1. ICU patients in the acute phase of critical illness after gastrointestinal oncological surgery 2. Age ≥18 years 3. Central venous access available for continuous infusion of the study drugs 4. Admitted to the ICU during the previous 24 h with a minimum expected ICU stay of ≥5 days 5. Sequential Organ Failure Assessment (SOFA) score ≥ 2 6. Written informed consent from the patient or the patient’s legal representative	Exclusions associated with nutritional status: 1. Received parenteral nutrition within 7 days before randomisation 2. Expected to receive ≥20% of energy via supplemental EN and/or non-nutritional sources (e.g. glucose solution for drug dilution or lipids from propofol) during the first 3 nutritional treatment days 3. Inability to initiate EN prior to randomization 4. Body mass index <17 kg/m^2^ or >35 kg/m^2^ 5. Any congenital errors of amino acid metabolism Exclusions associated with comorbidities and allergies: 6. Known hypersensitivity to fish, egg, soybean proteins, peanut proteins, or to any of the active substances or excipients contained in SPN 7. Known hypersensitivity to milk protein or to any other substance contained in SPN 8. Hemophagocytic syndrome 9. Known history of HIV, hepatitis B and/or C 10. Any severe, persistent blood coagulation disorder with uncontrolled bleeding Concomitant therapy exclusions: 11. Chronic maintenance therapy with systemic glucocorticoid steroids (hydrocortisone >0.3 mg/kg/d). 12. Concomitant administration of chemotherapy 13. Administration of growth hormone and teduglutide within the previous 4 weeks	Laboratory exclusions: 14. Hypertriglyceridemia characterised by serum triglyceride levels >4 mmol/L (>350 mg/dL) 15. Treatment-refractory, clinically significant major abnormality in the serum concentration of any electrolyte (sodium, potassium, magnesium, total calcium, chloride, inorganic phosphate) 16. Acute liver failure with encephalopathy, including intoxication (e.g. paracetamol, death cap, golden chain) and/or liver enzymes (aspartate aminotransferase, alanine aminotransferase, gamma glutamyl transferase) or bilirubin exceeding 10 x upper limit normal Other exclusions: 17. Chronic liver failure (Child-Pugh scale B or C), e.g. secondary to drug or alcohol abuse 18. Participation in another interventional clinical trial within the previous 4 weeks 19. Pregnancy or lactation 20. Previous inclusion in the present study 21. Patient unlikely to survive to 6 months due to underlying illness 22. Receiving end-of-life-care

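### The day-3 threshold for enteral intolerance (60% of protein needs) conflicts with the early-SPN feeding plan (enteral share up to 20%), so the endpoint partly records allocation

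*Protocol article*

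**What the plan says.** The Secondary endpoints section of the protocol article opens a list headed "During the 7-day treatment period in both treatment arms" with "EN route intolerance (inability to administer up to 60% of protein needs on day 3 via EN route". The Statistical analysis section assigns dichotomous secondary outcomes to a chi-square test.

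The feeding plans are these:

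- **Intervention group:** "The intervention group will receive EN reaching up to 20% of daily nutritional requirements". SPN supplies up to 80% of protein and calories from day 1, "which will be continued until day 7 of ICU stay for the purpose of the study". The protein target is 2 g/kg/day, or 2.5 g/kg/day under CRRT.
- **Control group:** "The control group will receive EN reaching up to 20% of their daily nutritional requirements". The protein targets are the same, and SPN is given "on day 7 of ICU stay if it is not already met via EN".
- **Abstract, Methods:** controls receive no parenteral supplement until day 7 "while enteral nutrition is gradually increased".
- **Dosage:** the SPN dose is lowered when energy comes from EN, oral intake or non-nutritional sources.
- **Table 1, exclusion 2:** "Expected to receive ≥20% of energy via supplemental EN and/or non-nutritional sources" during the first three nutritional treatment days.

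**The concern.** An intolerance endpoint should separate patients whose gut does not accept feed from those whose gut does. Here the threshold is a fraction of total protein needs, while the share of needs that is meant to go by the enteral route is itself set by the allocated plan. In the early-SPN arm that share is one third of the threshold, so a patient can be classed as intolerant simply because the plan was followed.

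The chi-square comparison of this endpoint is therefore at stake. Depending on how controls are fed by day 3, it would either have almost nothing to compare or show an excess of intolerance under early SPN that comes from the feeding plan. The second outcome is the more harmful, because it could be reported as an adverse effect of the intervention.

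**Working it through.** The article states no event rate for this endpoint, so there is no figure to reproduce. The check sets the feeding plan against the threshold on the article's own targets.

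**Inputs.** EN share 20%, SPN share 80%, and protein targets of 2 and 2.5 g/kg/day (Intervention group). Threshold 60% on day 3 (Secondary endpoints). 110 patients per arm (Sample size).

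**Step 1: planned EN against the threshold in the early-SPN arm.**

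| Target (g/kg/day) | Planned EN, at most (20%) | Threshold (60%) | Ratio |
|---|---|---|---|
| 2.0 | 0.20 × 2.0 = 0.4 | 0.60 × 2.0 = 1.2 | 1 to 3 |
| 2.5 (CRRT) | 0.20 × 2.5 = 0.5 | 0.60 × 2.5 = 1.5 | 1 to 3 |

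The shortfall is 60 − 20 = 40 percentage points of protein needs.

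**Step 2: could an early-SPN patient reach 60% while on the planned SPN?** The planned shares already sum to 20% + 80% = 100%, and day 3 lies within days 1 to 7. EN at 60% with SPN at 80% would be 140% of target: 2.8 g/kg/day, or 3.5 under CRRT. To stay within target, SPN would have to fall to 100% − 60% = 40% (0.8 or 1.0 g/kg/day), half its planned maximum. Nothing in the article directs early-arm EN towards 60% by day 3.

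**Step 3: the control arm.** The first clause of the Control group section gives up to 20%. The abstract's gradual increase, and the clause that makes day-7 SPN conditional on needs not being met by EN, make sense only if EN can go beyond 20%. No day-3 level is given, so both readings have to be followed through.

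**Step 4: consequence for the comparison.** Assume that all 110 early-SPN patients are assessed on day 3 and fed as planned, so that all count as intolerant. Let k of 110 controls reach 60%. The uncorrected chi-square statistic is then

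220 × (110k)² / [110 × 110 × (220 − k) × k] = 220k / (220 − k).

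- k = 0 (20% holds for controls too): every patient is an event, and no comparison is possible.
- k = 11 (10% of controls, assumed): 2420 / 209 = 11.58.
- k = 55 (50% of controls, assumed): 12100 / 165 = 73.33.

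The 5% critical value on one degree of freedom is 3.84. The apparent difference in intolerance equals k/110, with no difference in true tolerance required. The values of k are illustrations, because the article gives nothing from which to estimate it.

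**The case against.** The strongest reply is that 20% is not a protocol-wide ceiling. A reader might infer that it is, and that every patient in both arms will be classed as intolerant. The documents do not support that. The abstract and the conditional day-7 clause let control EN rise, and the Dosage section lowers SPN when EN supplies energy, so 20% is not an absolute limit even in the early arm. This stands. The conflict is firm for an early-SPN patient fed as planned; for controls there is only an inconsistency.

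A reader might also take exclusion 2 as proof that 60% is unreachable by design. It is not. It concerns energy expected at screening, from EN and non-nutritional sources together, and does not limit the protein delivered by EN after randomisation. It makes 60% less likely and no more than that.

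Third, the definition speaks of inability, so a patient who was never offered more feed has arguably not shown it. That is a fair reading, but the definition gives no rule for telling planned restriction from failure to tolerate. Nor is the threshold wording clear, since any amount from zero to 60% is up to 60%.

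Finally, a condensed article may leave a day-by-day EN schedule to the full protocol, so its absence is no error. The point does not rest on that absence. It rests on a stated definition that conflicts with a stated feeding plan.

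**Conclusion.** The concern holds in this form: the 60% threshold conflicts with the early-SPN feeding plan by a factor of three, at either protein target. Under adherence to that plan, an early-SPN patient is below the threshold regardless of tolerance.

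The effect on the comparison depends on control-arm EN, which the article states inconsistently. If it rises by day 3, the endpoint partly measures allocation and is biased towards more intolerance under early SPN; the size of that bias cannot be fixed from the article. If it stays at 20%, the endpoint carries almost no information. An event rate near 100% in both arms follows only under the second reading, and should not be presented as what the protocol implies.

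This should be corrected, but it does not threaten the trial. It affects one of 15 secondary endpoints, for which the article gives no ranking. The primary outcome (SF-36 physical component score), its analysis and the sample size are unaffected.

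**What to change.** 1. Redefine the endpoint so that it does not turn on the allocated feeding plan. The Treatment and support in-hospital data section already provides for recording intolerance to EN or PN and any decrease or discontinuation of nutritional support. Use recorded intolerance to EN, and EN decrease or discontinuation because of it, under one written rule applied identically in both arms.
2. Report EN received relative to EN target volume only as a descriptive supplement. A threshold on that ratio (for example, 60% of the EN prescribed) would not cure the problem: the target may differ by arm, and unblinded staff could lower it when feeding goes badly.
3. Replace the unclear threshold wording. If any threshold is kept, state plainly whether the event is reaching it or failing to reach it.
4. Reconcile the abstract's Methods, the Intervention group, Control group and Dosage sections, exclusion 2 in Table 1 and the endpoint definition. Which enteral level is right is for the sponsor.

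**Cost.** A change of endpoint wording, a short recording rule and acceptance by the local ethics committees. The data items are already planned, though the record should show why EN was reduced. The endpoint ceases to be a simple protein threshold and relies on intolerance recorded by staff who, as the Blinding section says of investigators, cannot be masked. If control EN does rise, controls also have more enteral exposure in which to show intolerance, so the EN received should be reported beside the result.

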### Sample size

Target sample size: 220 (110 in each intervention and control group).

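### The day-3 threshold for enteral intolerance (60% of protein needs) is out of line with the roughly 20% enteral level that the entry criteria and feeding plan imply

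*Protocol article*

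**What the plan says.** Under Secondary endpoints, the first item in the block headed "During the 7-day treatment period in both treatment arms" is "EN route intolerance (inability to administer up to 60% of protein needs on day 3 via EN route". I read this as failure to reach 60% of protein needs by EN on day 3.

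Four other places bear on how much EN a patient can be receiving that day:

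- **Table 1, exclusion 2** removes patients "Expected to receive ≥20% of energy via supplemental EN and/or non-nutritional sources" "during the first 3 nutritional treatment days". That window includes day 3, and glucose diluent and propofol lipid count toward the 20%.
- **Intervention group:** "The intervention group will receive EN reaching up to 20% of daily nutritional requirements". Up to 80% comes from supplemental parenteral nutrition (SPN) from day 1 to day 7.
- **Control group:** the same 20% EN level is stated, with SPN on day 7 only where EN has not by then covered needs. The abstract adds that "the control group is not supplemented parenterally until the seventh day of ICU stay while enteral nutrition is gradually increased".
- **Dosage:** when energy comes from other sources, including EN, "the dose of the SPN will be reduced accordingly".

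Statistical analysis assigns a chi-squared test to dichotomous secondary outcomes.

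**The concern.** The endpoint is meant to show whether the gut tolerates feeding, but its cut-off is three times the EN level that the Intervention group and Control group sections describe. It also falls inside the period for which exclusion 2 selects patients expected to receive little EN. A patient fed as those sections describe would be scored as an event without tolerance having been tested.

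Two outcomes are possible. Either nearly all patients in both arms are events and the comparison says nothing, or one arm's EN is raised and the other's is not, and part of any difference is the feeding plan itself. In the second case a reader could mistake assigned dose for a treatment effect on gut tolerance.

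**Working it through.** The document gives no event rate, power or sample size for this endpoint, so there is no stated figure to reproduce. The check asks whether EN at 20% can supply 60% of protein needs.

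**Inputs**
- Protein need 2 g/kg/day, or 2.5 g/kg/day on continuous renal replacement therapy (CRRT); energy 15–20 kcal/kg/day (Intervention group, Control group).
- Guideline energy range 20–25 kcal/kg/day (Background, Overview), used as a sensitivity range.
- Assumed: 4 kcal per g of protein; a mixed feed with 20–30% of its energy as protein.

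**Direct reading.** If 20% of requirements applies to protein as well as energy, EN supplies 20% of protein needs, one third of the threshold (20/60).

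**Threshold in energy terms.** 0.60 × 2 = 1.2 g/kg/day; 1.2 × 4 = 4.8 kcal/kg/day as pure protein.

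**What 20% of energy can carry.** EN protein = 0.20 × energy target × protein share ÷ 4.

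| Energy target (kcal/kg/day) | Protein share of feed energy | EN protein (g/kg/day) | Share of 2 g/kg |
|---|---|---|---|
| 15 | 20% | 3 × 0.20 ÷ 4 = 0.15 | 7.5% |
| 20 | 20% | 4 × 0.20 ÷ 4 = 0.20 | 10% |
| 20 | 30% | 4 × 0.30 ÷ 4 = 0.30 | 15% |
| 25 | 30% | 5 × 0.30 ÷ 4 = 0.375 | 18.75% |
| 15 | 100% (bound) | 3 ÷ 4 = 0.75 | 37.5% |
| 20 | 100% (bound) | 4 ÷ 4 = 1.00 | 50% |
| 25 | 100% (bound) | 5 ÷ 4 = 1.25 | 62.5% |

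At the trial's own energy target, even an all-protein feed falls short of 60%. At 25 kcal/kg/day the threshold fits only if 4.8 ÷ 5 = 96% of EN energy is protein. So the fact that exclusion 2 speaks of energy and the endpoint of protein does not reconcile the two.

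**EN needed to reach the threshold.** With the assumed feeds, 4.8 ÷ 0.30 = 16 to 4.8 ÷ 0.20 = 24 kcal/kg/day. That is 80–160% of a 15–20 kcal/kg target (16/20 to 24/15), or 64–120% of a 20–25 kcal/kg target (16/25 to 24/20).

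**CRRT.** 0.60 × 2.5 = 1.5 g/kg/day, or 6 kcal/kg/day as pure protein: 30–40% of 15–20 kcal/kg and 24–30% of 20–25 kcal/kg, above 20% throughout.

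**Consequence for the test.**
- Both arms near 20% EN: event rate near 100% in each, so the chi-squared test has nothing to compare.
- Control EN raised, intervention EN not: some control patients may cross 60% because they were given more EN. As an extreme illustration only, take the planned "Target sample size: 220 (110 in each intervention and control group". Suppose all 110 intervention patients stay at 20% and are scored intolerant, while 6 controls reach 60%. Then 110/110 against 104/110 gives chi-squared = 220 × (110 × 6)² ÷ (110 × 110 × 214 × 6) = 6.17, p = 0.013 (0.038 with continuity correction). This shows how few patients could separate the arms; it does not forecast that they will.

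**The case against.** The best defence is that nothing caps EN at 20%. Exclusion 2 is a forecast at entry and does not limit delivery. The Control group section uses the same 20% wording as the intervention section, yet allows that EN alone may meet needs by day 7, so 20% reads more naturally as a starting level. The Dosage section lets SPN fall as EN rises, and no sentence tells staff to hold intervention EN down against tolerance. Some patients could therefore pass 20%, and some could reach 60%.

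That stands, and it rules out two stronger readings. A reader might infer that the endpoint measures only entry and assignment and never tolerance. The documents do not support this, because EN can rise, explicitly so in control. A reader might also infer that the comparison is biased against early SPN. That requires intervention EN to stay at 20% while enough control EN rises to 60% by day 3. The contrast between arms rests mainly on one clause in the abstract, and the arithmetic above shows how much EN a control patient would need. A near-100% rate in both arms is at least as likely.

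The defence does not remove the misalignment. The trial selects patients expected to be far below the cut-off on day 3, and anyone who follows that expectation is an event by definition. Taking inability to require a real attempt does not help either: a patient left at 20% was not tested and cannot be classified.

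**Conclusion.** The point holds as a misalignment between one secondary endpoint and the plan around it. A patient at about 20% EN on day 3 receives roughly 7.5–19% of protein needs from a mixed feed, against a 60% cut-off, and is classed as intolerant regardless of gut tolerance. The result is either uninformative (both arms near 20%) or partly driven by assigned feeding (control EN escalated alone). The document does not fix which, nor the direction or size of any distortion.

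The percentages rest on 4 kcal/g, a feed with 20–30% of energy as protein, and 2 g/kg/day as the total protein need. At the trial's own energy target the shortfall holds for any feed composition.

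This should be corrected, but its reach is small: it is one of fifteen secondary endpoints, and the primary endpoint and sample size are not affected.

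**What to change.** Amend the Secondary endpoints section before outcome data are seen:

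1. Stop using the 60% threshold to define intolerance. Report the percentage of protein needs given by EN on day 3 descriptively, within the existing protein-delivery endpoint.
2. Define EN intolerance as EN reduced or stopped because of recorded intolerance on any of days 1 to 3.
3. Show that result together with EN received against the EN target volume for each patient.
4. State two limitations with the result. Staff judging intolerance know the allocation, since the Blinding section says investigators cannot be masked. Patients assigned less EN also have less opportunity to show intolerance, which could favour early SPN if its EN stays low. A between-arm difference should therefore not be read as a pure tolerance effect.

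Exclusion 2 and both feeding regimens can stay as they are.

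The cost is one amendment to one secondary endpoint. Treatment and support in-hospital data already lists target and received volumes, intolerance, and reduction or stopping of support. If the form does not record why EN was reduced, one field must be added. The price is that a measured quantity gives way to an unblinded judgement that still depends on EN dose, which is why steps 3 and 4 belong with the change.
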